## Abstract

**Introduction:**

Physical activity has important benefits for the prevention and management of chronic diseases and healthy ageing. Health professionals have valuable opportunities to promote physical activity to a large group of people across the lifespan. Promotion of Physical Activity by Health Professionals is a hybrid type 1 effectiveness-implementation cluster randomised trial designed to evaluate the impact of physical activity promotion by health professionals (n=30 clusters) on physical activity participation in their patients (n=720). To inform the future implementation of this programme, we will be conducting a within-trial and modelled economic evaluation.

**Methods and analysis:**

We will conduct a cost-effectiveness and cost-utility analysis from the perspective of the healthcare, aged care and disability funder. The time horizon will be 6 months for the within-trial analysis and 2 years for the modelled analysis. Data on intervention costs will be collected using trial records. Data on healthcare utilisation will be collected using data linkage. Incremental cost-effectiveness ratios (ICERs) will be reported for physical activity and quality-adjusted life years outcomes. Bootstrapping will be used to explore uncertainty around the ICERs and estimate 95% CIs. Results will be presented on a cost-effectiveness plane. The probability that the intervention would be cost-effective at varying willingness-to-pay thresholds will be presented using a cost-effectiveness acceptability curve.

**Ethics and dissemination:**

Ethics approval was obtained through Sydney Local Health District (RPAH zone) Ethics Review Committee (X23-0197). The findings of this study will be disseminated through peer-reviewed journal articles and conference presentations.

**Trial registration number:**

Australian New Zealand Clinical Trials Registry: ACTRN12623000920695.

STRENGTHS AND LIMITATIONS OF THIS STUDYThis protocol contributes to the current limited body of evidence on the cost-effectiveness of implementation strategies supporting health professionals to promote physical activity to their patients and follows best practice recommendations for conducting and reporting an economic evaluation alongside a trial.Within-trial and modelled analysis will be conducted to capture costs and health outcomes over an extended timeframe, providing evidence for the long-term cost-effectiveness of implementation support for physical activity promotion.The use of preference-based utility scores (from EuroQol 5-dimensions 5-level version) will facilitate decision-making when comparing programmes for funding.The use of data linkage for healthcare utilisation costs overcomes the limitations of self-reported measures of service utilisation and will allow for a greater understanding of costs from a range of perspectives.The main effectiveness outcome—physical activity participation—is a self-reported measure and may be subject to recall bias.

## Introduction

 Physical activity (PA) has a multitude of health benefits, including reducing mortality and aiding in the prevention and management of chronic diseases such as cardiovascular disease, diabetes and cancer.^1^ However, physical inactivity remains a pressing global health issue, leading to 5.3 million avoidable deaths annually.^2^ To address this issue, the evaluation and widespread implementation of suitable PA interventions are urgently needed.

International organisations such as the WHO and International Society for Physical Activity and Health have advocated for PA promotion to be integrated into healthcare settings, with health professionals holding a valuable opportunity to promote PA to a large group of people across the lifespan.^3 4^ Health professionals themselves have indicated a strong interest in supporting their patients to be more active.^5 6^ However, this is limited by a number of reported barriers to providing this support, such as limited skills in facilitating behaviour change, a lack of suitable local PA options and limited knowledge of and trust in available community-based PA programmes.^5 7^

In this context, the *Promotion of PA by Health Professionals (PROMOTE-PA)* trial is a hybrid type 1 effectiveness-implementation cluster randomised trial that has been designed to investigate the effect of PA promotion by health professionals (n=30 clusters) with support from a research team on PA levels among patients (n=720) receiving care in outpatient or community settings.^8^ In addition to determining the effectiveness of the implementation strategies, decision makers will likely also be interested in whether the intervention represents value for money when considering implementation.^9 10^

Therefore, the objective of this study is to conduct an economic evaluation of PA promotion supported by implementation strategies compared with usual care of patients, with a view to inform implementation of similar programmes in other healthcare settings in the future.

### Economic questions

Primary:

From the perspective of healthcare, aged care and disability care funders, what is the cost-effectiveness and cost-utility (incremental costs and health outcomes in terms of PA and quality-adjusted life years (QALYs)) of PA promotion by health professionals with support from the research team compared with usual care over 6 months?

Secondary:

From the perspective of the healthcare funder, what is the cost-effectiveness (incremental costs and health outcomes in terms of PA promotion by health professionals (implementation outcome)) of PA promotion by health professionals with support from the research team compared with usual care over 6 months?What is the level of healthcare utilisation among patients of health professionals receiving support for PA promotion compared with usual care over 2 years?From the perspective of healthcare, aged care and disability care funders, what is the cost-effectiveness and cost-utility (incremental costs and health outcomes in terms of PA and QALYs) of PA promotion by health professionals with support from the research team compared with usual care over 2 years?

## Methods

An economic evaluation of a hybrid type 1 effectiveness-implementation randomised controlled trial will be conducted. A within-trial analysis will be conducted over the 6-month duration of the trial and a modelled analysis over 2 years. Healthcare utilisation over 2 years will also be reported. The trial is described briefly below; details can be found in the trial protocol published separately.^8^

### *PROMOTE-PA *trial

#### Study population

Patient participants will be 720 individuals aged 5 years and above living in the community who are receiving outpatient care from health professionals (n=30 clusters) at one of the multiple participating local health districts, a specialty children’s health network or a private clinic in New South Wales, Australia.

Study recruitment commenced in February 2024 and is expected to finish by December 2025. Participant follow-up is expected to be completed in December 2026.

#### Patient and public involvement

This study was codesigned with clinical and health service manager investigators. The implementation strategies were developed and refined with local health professional input, via semistructured interviews and focus groups during part I of *PROMOTE-PA* as well as previous surveys, interviews and consultations with health professionals and patients conducted by our group. A *PROMOTE-PA* consumer advisory group has been established for this study. Members have provided feedback on the development of study information and consent forms, participant surveys and educational resources for patients. This feedback has been used to further develop trial information and consent forms. Further details around consumer and health professional input can be found in the published trial protocol.^8^ Health professional and patient participants will be able to indicate whether they wish to receive a report of the study in the participant consent form.

#### Intervention(s) and comparator(s)

##### Intervention

As this economic evaluation is being conducted alongside an effectiveness-implementation trial, there are two components being investigated: (1) the delivery of implementation strategies to health professionals delivering outpatient and community-based care and (2) the delivery of PA promotion by health professionals to their patients (children aged 5 years or older and adults). The implementation strategies and PA promotion intervention are outlined briefly below and are further described in the trial protocol.^8^

##### Implementation strategies

The research team will deliver PA promotion support to health professional (clinical) teams using a range of implementation strategies. The implementation strategies will be tailored to each team as part of an initial service mapping process. During service mapping, the research team, together with clinical teams and managers, will collaboratively identify factors relevant to the implementation process in their clinical context and the most suitable implementation strategies to be delivered to each team. The frequency of support provided by the research team to clinical teams will vary according to the needs of each team. All teams will receive access to an online education and training resources hub, with additional implementation strategies described below:

Community PA referral support: this may include assistance to find suitable PA opportunities and develop referral systems as well as contact with community PA opportunities from the research team.Experts and clinical mentors: individuals external to the clinical team sharing their experience on PA promotion (eg, through presentations and questions and answers).Clinical champions: individuals who are part of the clinical teams supporting implementation of PA promotion as part of routine practice.

##### PA promotion

Health professional teams will be asked to deliver PA promotion during at least one session to each patient participant as part of routine clinical practice using the 5As promotion model.^11^ All health professional teams will be advised to undertake the first component (assess their patients), with the remaining four components adopted depending on each clinical team’s implementation strategy. The 5As model includes the following components: (1) *Assess* patients’ PA levels and barriers and facilitators to participation, then provide brief PA advice; (2) *Advise* on benefits of PA and make tailored PA recommendations to their patients; (3) *Agree* on PA goals and develop a PA action plan with the patient; (4) *Assist* patients to identify physical activity barriers and potential solutions and set up a self-monitoring strategy; (5) *Arrange* patient referral to a PA programme, social support or follow-up.

Where clinical teams have limited capacity to deliver PA coaching as part of routine practice, patient participants will be invited to participate in the *PROMOTE-PA* Linkage Programme which provides up to two sessions of telehealth PA coaching to patients. Further details about this programme can be found in the trial protocol.^8^ Additional PA programmes that support patients transitioning from hospital to community-based PA programmes may be developed as required.

##### Comparator

Health professionals in the waitlist control group will not receive additional support to increase PA promotion to their patients during the control period and will continue to deliver usual care. Implementation support will be provided to these clinical teams after they have completed recruitment of their patient participants during the control period (figure 1).

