### Economic evaluation overview

This economic evaluation will be conducted from the healthcare, aged care and disability care funders’ perspective. All costs will be valued in 2024 $A. Within-trial cost-effectiveness and cost-utility analysis will be conducted as part of the *PROMOTE-PA* study, to determine the incremental costs and incremental health outcomes of the implementation strategies for PA promotion compared with usual care. Data linkage will be used to determine and compare levels of healthcare utilisation among patients of health professionals receiving support for PA promotion compared with usual care over 2 years. Decision-analytical modelling will be used to determine the incremental costs and health outcomes with an extended time horizon of 2 years. The economic evaluation will be reported according to the Consolidated Health Economic Evaluation Reporting Standards.^12^ A statistical analysis plan for the within-trial and modelled analyses will be written and signed by the study authors prior to the commencement of data analysis.

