### Within-trial analysis

The time horizon for the within-trial analysis is 6 months, representing the length of follow-up for patient participants in the trial. Costs and health outcomes will not be discounted as the time horizon is less than 12 months. The analysis will follow an intention-to-treat approach.

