The health professional-level outcome (secondary question) used will relate to the level of PA promoted by health professionals, captured using self-reported study-specific surveys including questions about health professionals’ PA promotion behaviours at baseline and 6-month follow-up. The effectiveness outcome measure for this within-trial cost-effectiveness analysis will be the change in PA promotion in the intervention group compared with the control group at 6 months.

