### Comparison of resource utilisation

The primary resource utilisation outcomes will be rates and cost of healthcare, aged care and disability service utilisation in both groups over 2 years. A breakdown of healthcare utilisation costs according to cost categories (emergency, admitted, non-admitted and ambulance data, Medicare Benefits Schedule/Pharmaceutical Benefits Scheme, NDIS and aged care services use) will also be reported.

Healthcare, residential aged care and disability resource utilisation and costs will be described using means, SD, medians and IQRs over the 2-year period. Rates of service use will be compared between groups using negative binomial regression.

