#### Model structure

A Markov model will be used to explore the long-term cost-utility of the implementation strategy with uptake and outcome data (at 6 months) from the trial. A working group will be established to define the parameters to be used in the modelled analyses. In the model, the trial cohort will be followed over 2 years. A cycle length of 3 months will be used. The 2 year healthcare, residential aged care and disability service utilisation costs will be acquired through data linkage and supported by costs reported in the published literature.

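### The 2-year comparator is called usual care, but control teams may receive the support during much of that window

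*Protocol article*

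**What the plan says.** Under Comparator, usual care is assured for a limited time only: "Health professionals in the waitlist control group will not receive additional support to increase PA promotion to their patients during the control period". The next sentence says when it ends: "Implementation support will be provided to these clinical teams after they have completed recruitment of their patient participants during the control period". It gives no interval between the end of recruitment and the start of support, and does not mention the end of follow-up. The Figure 1 caption speaks of early and delayed support groups.

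The 2-year analyses are worded differently. A secondary economic question asks: "What is the level of healthcare utilisation among patients of health professionals receiving support for PA promotion compared with usual care over 2 years". The Economic evaluation overview repeats this for the linked data: "compare levels of healthcare utilisation among patients of health professionals receiving support for PA promotion compared with usual care over 2 years". A further secondary question asks for 2-year cost-effectiveness and cost-utility, again against usual care. Comparison of resource utilisation states: "The primary resource utilisation outcomes will be rates and cost of healthcare, aged care and disability service utilisation in both groups over 2 years". It plans negative binomial regression between groups and does not separate time before and after a control team is supported.

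Model structure takes outcome data from the trial at 6 months, while "The 2 year healthcare, residential aged care and disability service utilisation costs will be acquired through data linkage", supplemented by published costs. The health-professional outcome rests on surveys with "questions about health professionals’ PA promotion behaviours at baseline and 6-month follow-up". The limitations in the Discussion cover differential recruitment but not later support of the control teams.

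**The concern.** A patient's 2-year window starts at that patient's recruitment. Support for the control team is triggered when the team's recruitment ends. Unless the unstated lag is very long, the trigger falls inside the window of many control patients. From then on, the randomised contrast is between teams supported early and teams supported late.

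Two things are at stake. First, if control patients go on seeing a supported team, the 2-year utilisation difference would most likely be pulled towards zero. A null result would then fit either no effect or convergence once both groups were supported. Second, if arm-specific linked costs feed the model, the 2-year cost-utility ratio could combine an effect of supported against unsupported teams with a cost difference between early and delayed support. Funders reading it as value against usual care would be reading a different quantity.

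**Working it through.** The article gives no figure on this point to reproduce. The check is timeline arithmetic.

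**Inputs**
- Horizon H: 24 months (Economic questions) and 6 months ("The time horizon for the within-trial analysis is 6 months, representing the length of follow-up for patient participants in the trial").
- Recruitment duration of a control team, r: not stated. The Study population section gives February 2024 to December 2025, about 12 + 10 = 22 months, as a ceiling. Assumed values: 3, 6, 12 and 22.
- Lag from a team's last recruit to its support start, L: not stated. Assumed values: 0, 3, 6 and 12 months.
- Fraction q of control patients still seen by the team after support starts: not stated.

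**Formula.** With even recruitment, a patient recruited at month t has u = r + L − t months before support and max(0, H − u) after it. Averaged over t:
- if r + L ≤ H, mean post-support time = H − L − r/2;
- if L < H < r + L, it is (H − L)²/(2r);
- if L ≥ H, it is 0.

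**Examples, H = 24**
- r = 3, L = 0: 24 − 1.5 = 22.5 months; 22.5/24 = 93.8%.
- r = 12, L = 6: 24 − 6 − 6 = 12 months; 12/24 = 50.0%.
- r = 22, L = 12: 12²/44 = 3.27 months; 3.27/24 = 13.6%.

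**Share of control person-time after the team's support starts**

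| r (months) | 24-month window: L = 0 | L = 6 | L = 12 | 6-month window: L = 0 | L = 6 or more |
|---|---|---|---|---|---|
| 3 | 93.8% | 68.8% | 43.8% | 75.0% | 0% |
| 6 | 87.5% | 62.5% | 37.5% | 50.0% | 0% |
| 12 | 75.0% | 50.0% | 25.0% | 25.0% | 0% |
| 22 | 54.2% | 30.7% | 13.6% | 13.6% | 0% |

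**From team time to patient exposure.** Exposed time is about q times the share. With r = 6, L = 0 and q = 0.25 (illustrative), 0.25 × 87.5% = 21.9%; with q = 0 it is nil.

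**Six-month assessments.** The fraction falling after support is min(1, (6 − L)/r) for L below 6, and 0 otherwise. At L = 0 it is 100% for r = 3 or 6, 6/12 = 50% for r = 12, and 6/22 = 27.3% for r = 22. At L = 3 it is 100%, 50%, 25% and 13.6%. If the health professionals' survey clock starts with the team's recruitment (assumed), the 6-month survey falls after support only when r + L is below 6.

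**Model inputs side by side.** At r = 12 and L = 6, none of the 6-month effect window is post-support, but half of the 24-month cost window is. This is how effects and costs can come to refer to different comparators.

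**The case against.** A reader might infer that control teams are supported the moment recruitment closes, that control-arm costs therefore do not represent usual care, and that the 2-year contrast is diluted by some stated percentage. The article does not support any of these. It says support comes after recruitment, without a lag; Figure 1 and the separate trial protocol, neither of which is available here, may give the timing. Support goes to teams, and a control patient is affected only by continuing to attend and then receiving promotion. The intervention asks for at least one session, and nothing says how long patients remain in care. Many may have been discharged. Any dilution percentage needs a contact rate that no document supplies.

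On the model, published literature also informs costs, a working group will set the parameters, and the article does not say that costs enter by arm. A mismatch is possible, not established. With a lag of 6 months or more, the 6-month patient window is clean.

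A signed analysis plan is promised, and censoring rules belong there. That excuses the lack of a rule. It does not excuse the label: the article itself names the 2-year comparator as usual care while describing a control group that moves to support on a recruitment trigger. All these limits on the size of the problem stand; the mislabelled contrast remains.

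**Conclusion.** The point holds in limited form. The 2-year contrast as named is not the one the design assures, and a null 2-year utilisation result could not be read as no effect against usual care. Post-support team time is about 14% to 94% of control 24-month person-time across the assumed grid (even recruitment over 3 to 22 months, lag 0 to 12 months). Each share is an upper bound on patient exposure in its scenario; true exposure could be far smaller, even nil. The model's costs and effects may refer to different comparators, depending on how the linked costs are used. The 6-month outcomes and staff surveys are at risk only if support starts before those assessments are complete.

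Severity is moderate: the 2-year questions are secondary, and the primary 6-month analysis is affected only under a short lag.

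**What to change.** 1. In the economic questions, the overview and the resource utilisation section, describe the 2-year utilisation comparison as early versus delayed support. State that a null result will not be read as no effect against usual care.
2. Log each control team's support start date. Where the linked data allow, record control patients' later contact with that team.
3. Keep the intention-to-treat 2-year comparison. Add a pre-specified supplementary analysis that censors control person-time at support start, applies a matched window in the early group, and reports how much control time remains.
4. In the model, do not treat post-support control costs as usual care without a scenario analysis using pre-support control costs, the published costs the plan already allows, or both.
5. At 6 months, report how many control assessments and staff surveys postdate support. Run a sensitivity analysis excluding them only if enough remain.

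The cost is some wording, one date per control team and a few added analyses; randomisation and the main analyses are untouched. The supplementary results may be imprecise. At r = 6 and L = 0, only 24 − 21 = 3 months of control time per patient remain (3/24 = 12.5%), too little to supply 2-year usual-care costs alone, and no control 6-month assessment would survive exclusion. Items 3 to 5 therefore supplement the main analyses and do not replace them.
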